### Planned Analysis

#### Qualitative Analysis

To analyze the qualitative data, an exploratory approach within an applied thematic analysis framework will be used in this study. Following the 6 phases of thematic analysis of Braun and Clarke [27], the process will begin with familiarization through repeated readings of the interview transcripts and initial memo writing to capture early analytic impressions. In the next stage, initial codes will be generated inductively from the data. Codebooks will be developed separately for client and practitioner transcripts, allowing codes to reflect participant language and meaning while attending to the study’s focus on the accessibility, experience, and value of ShockTalk.

After coding, the research team will search for themes by collating related codes into broader categories that capture patterned responses across the dataset. These candidate themes will then be reviewed for coherence and consistency within and across transcripts. To enhance rigor, 2 researchers will independently code transcripts, and coding decisions and candidate themes will be refined collaboratively during team meetings.

In the defining and naming stage, themes will be further refined to ensure clear boundaries and internal coherence, and concise names and definitions will be developed to represent their essence. Finally, the reporting phase will involve weaving together the analytic narrative with illustrative quotations from participants to demonstrate how themes capture client and practitioner perspectives on ShockTalk’s accessibility, user experience, and value, and to link these findings back to the research objectives.

#### Cost Analysis

Given the pilot nature and limited sample size of this study (n=10), the economic evaluation is not designed to conduct a formal cost-effectiveness analysis. Instead, the cost analysis is focused on assessing the feasibility of cost data collection, identifying relevant cost components, and reporting preliminary, descriptive cost estimates across varying levels of engagement with the ShockTalk intervention.

We will adopt a health care provider perspective for this analysis, capturing the direct costs related to service delivery through the ShockTalk app. These costs will include (1) therapist compensation for up to 5 sessions per client, (2) platform use and administrative costs, and (3) personnel time involved in scheduling, coordination, and support. The time horizon for the analysis is 3 months, aligning with the study’s follow-up period.

Clients’ level of engagement will be characterized by treatment dose, defined as the number of therapy sessions completed during the 3-month period. Although we will descriptively report outcomes stratified by dose (eg, 1-2 sessions and 3-5 sessions), no inferential comparisons across groups will be made.

The primary outcome for exploratory effectiveness assessment in the cost analysis will be the change in client attitudes toward mental health treatment, as measured by the ATSPPH-SF. Secondary outcomes include trust in technology and telemedicine, measured via the PATAT, and client engagement, operationalized through session attendance and app interaction data.

This feasibility-focused cost analysis aims to determine the viability of collecting accurate and comprehensive cost and outcome data in a small-sample, community-engaged study context. Given the pilot nature of the study, these analyses are intended to test the feasibility of collecting cost data and to provide exploratory estimates to guide the design and analytic strategy for a future, fully powered economic evaluation.

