## Methods

### Overview

To test the feasibility of ShockTalk among Indigenous clients, we will conduct a small pilot study with 10 Indigenous therapy-seeking clients and 3 Indigenous mental health practitioners in Lenapehoking. This study was designed as a preliminary feasibility pilot to inform a larger trial and, therefore, was not prospectively registered.

After informed consent and baseline assessment, clients will be randomly allocated 1:1 to immediate access to ShockTalk (treatment) or to a 3-month waitlist control (5 clients per arm). The allocation list will be generated by a study team member not involved in enrollment and uploaded to a centralized randomization module, which will reveal the assignment only after baseline data entry. Allocation events will be logged. In the absence of a centralized system, sequentially numbered, sealed opaque envelopes prepared from the same allocation list will be used.

All participants will complete baseline surveys and a 3-month follow-up survey (3 months postrandomization). Waitlist participants will be offered access to the linkage-to-care intervention 3 months after their initial baseline survey is completed. Qualitative data collection at 3 months from baseline will include 1-hour semistructured interviews (Multimedia Appendix 1) with a purposive subsample of 5 clients (selected to reflect a range of engagement and experiences across arms) and a single focus group with participating practitioners. Finally, a preliminary cost analysis will be conducted using data from both arms to assess the feasibility of cost data collection and to generate exploratory cost estimates across varying levels of engagement. Analyses will be descriptive and feasibility-focused (ie, recruitment, retention, acceptability, and data completeness); inferential effectiveness claims will not be made given the pilot sample size.

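### The cost analysis claims data from both arms, but its 3-month horizon closes as waitlist access opens, so at most 5 of the 10 planned clients can inform cost by engagement; clients given access who complete no session have no named class.

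*Protocol article*

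**What the plan says.** The relevant statements, all in the protocol article, are these.

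- Methods, Overview, on data: "a preliminary cost analysis will be conducted using data from both arms". The stated purpose is to test whether cost data can be collected and to give exploratory estimates over a range of engagement.
- Methods, Overview, on design: clients go to immediate access "or to a 3-month waitlist control (5 clients per arm" planned). All complete a baseline survey and "a 3-month follow-up survey (3 months postrandomization").
- Methods, Overview, on access: "Waitlist participants will be offered access to the linkage-to-care intervention 3 months after their initial baseline survey is completed".
- Cost Analysis, on the horizon: "The time horizon for the analysis is 3 months", chosen to match the follow-up period.
- Cost Analysis, on dose: "defined as the number of therapy sessions completed during the 3-month period".
- Cost Analysis, on reporting: "we will descriptively report outcomes stratified by dose (eg, 1-2 sessions and 3-5 sessions"), with no inferential comparison between the classes.
- Cost Analysis, on size: "Given the pilot nature and limited sample size of this study (n=10"), given as the reason for not attempting a formal cost-effectiveness analysis.

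The cost components are therapist payment, platform and administrative charges, and staff time spent arranging and supporting care. The last two do not depend on a completed session.

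**The concern.** The horizon and the claim to use both arms do not fit together. A waitlist client has no access while the cost clock runs, so that arm cannot show variation in engagement, and engagement is what the estimates are meant to be reported against. A reader of the results could think that ten clients lie behind the cost-by-engagement figures when at most five can.

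The second part concerns the dose classes. The app exists to link people to care, so a client who is given access and never completes a session is an informative result. The section on how the app works describes one route to it: therapist and client decide at intake that they are not a fit, and the client is helped to find care elsewhere. That client uses platform and staff resources, yet neither example class can hold a count of 0. A 0-session class added without changing the clock would not settle this, because it would mix clients for whom linkage failed with waitlist clients who had not yet been offered it.

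At stake is how useful the pilot's cost description is. The article says the estimates will guide a later, fully powered economic evaluation, and the Quantitative Analysis section also relies on the dose groups when it speaks of balancing effect against cost.

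**Working it through.** **Inputs.** 10 clients, allocated 1:1 (Overview); horizon 3 months, matched to follow-up (Cost Analysis); follow-up dated from randomization (Overview); waitlist access at 3 months after baseline (Overview); dose = sessions completed within the 3 months (Cost Analysis); 4 clients enrolled (Results).

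**Step 1, the plan's own figure.** 10 / 2 = 5 clients per arm, as stated. There is no power calculation to reproduce.

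**Step 2, access inside the horizon.** Access time = end of horizon minus time at which access opens.

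- Immediate arm: 3 − 0 = 3 months per client, 5 × 3 = 15 client-months.
- Waitlist arm: 3 − 3 = 0 months per client, 5 × 0 = 0 client-months.

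This takes baseline and randomization as effectively the same date. Allocation follows the baseline survey, so a gap between them would open waitlist access before the horizon ends by the length of that gap. The article gives no gap.

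**Step 3, clients who can have a dose of at least 1.** 5 + 0 = 5 of 10, or 50%. This is a ceiling.

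**Step 4, how the ceiling falls.** Let p be the share of the immediate arm that completes at least one session. The article gives no value, so p is an assumption shown over a range. Clients who fit a named class = 5p; clients with dose 0 = 10 − 5p.

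| p (assumed) | Fit 1-2 or 3-5 sessions | Dose 0, of 10 | Of these, given access |
|---|---|---|---|
| 1.0 | 5 | 5 | 0 |
| 0.8 | 4 | 6 | 1 |
| 0.6 | 3 | 7 | 2 |
| 0.4 | 2 | 8 | 3 |
| 0.2 | 1 | 9 | 4 |

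The last column counts failed linkage. The other 5 dose-0 clients in every row are the waitlist, whose zero is fixed by the design.

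**Step 5, enrolment.** The Results section reports 4 clients and does not give the split by arm. If it was even, 4 / 2 = 2 clients could have a dose within the horizon.

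**Step 6, effect of moving the clock.** With the window opened at access, the waitlist window is months 3 to 3 + 3 = 6, and access time becomes 10 × 3 = 30 client-months in place of 15. All 10 planned clients can then be classified, including those with 0 sessions.

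**The case against.** Several points on the other side are sound.

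- **The classes are examples.** They are introduced by eg, a count of sessions can be 0, and final boundaries are the kind of detail an article may leave to a fuller document. A reader might infer that clients without a session, and their costs, are dropped. No sentence says so, and the listed platform and staff costs could capture them. The sentence on classes also refers to outcomes; it bears on costs only because the same section characterizes engagement by dose and reports costs by engagement.
- **No mean over ten clients is planned.** A reader might infer that costs will be averaged over both arms and so halved. The article uses n=10 only to describe the study's size and plans costs by level of engagement. Likewise, no specific understatement of cost per linked client can be claimed: that would need a non-linkage rate and a rule discarding overhead, and the article states neither.
- **A comparator with no intervention cost is not in itself a defect.** That is true, and including both arms may serve the aim of testing data collection. It does not supply estimates over a range of engagement, which is the other stated aim.
- **Another clock may be intended.** The Measures section times the second survey from treatment, and the Abstract admits five clients at 3 months. A horizon counted from each client's own access would give the waitlist a dose. The Overview and Cost Analysis read together do not support that, so the start of the horizon needs stating.
- **Later waitlist costs would lack outcomes.** This stands. The Ethical Considerations section lists two surveys only, at baseline and 3 months, so no ATSPPH-SF or PATAT score follows waitlist access.

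**Conclusion.** The concern holds as a conflict of timing together with a gap in classification. As written, all 5 waitlist clients have dose 0 by design, and at most 5 of the 10 planned clients can contribute session cost or a non-zero dose. Clients given access who complete no session are left unassigned.

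The conclusion rests on reading the 3-month horizon as the postrandomization follow-up, which is what the Cost Analysis and Overview sections say jointly, and on baseline and randomization falling close together. The severity is minor: the cost analysis is descriptive, makes no comparison between dose classes, and supports no effectiveness claim. What is affected is the denominator and content of the cost description passed on to the next study.

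**What to change.** In the Cost Analysis section:

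1. Count each client's 3-month cost and dose window from the date access opens: months 0-3 for the immediate arm and months 3-6 for the waitlist.
2. Add a 0-session class limited to clients given access, and say whether the 15-minute intake counts as a session.
3. Report cost per client given access and cost per client linked (at least one completed session), with the number given access stated as the denominator of the first.
4. State that waitlist clients contribute cost data only. Their 3-month survey precedes access, so their change score must not be paired with a dose from months 3-6.

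The cost is a few lines of text, some extra tabulation, and 3 further months of session and payment records for the waitlist arm. The study covers client sessions up to a limit, so payment records probably exist, but the article does not confirm that they reach past month 3. Data collection and analysis are reported as complete, so the change would be made in the results report. If the later waitlist records were not kept, the report should say that cost by engagement comes from the immediate arm alone and give that number.

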### Ethical Considerations

This study has been approved by the Columbia University Institutional Review Board (AAAU0850). The study coordinator will contact client and practitioner participants to determine their eligibility and to discuss the study purpose, risks, benefits, and compensation. During this meeting, the study coordinator will also obtain informed consent. Participants will be provided with an electronic version of the consent form and will be asked to sign and return the form at the end of the call.

Participants will be informed that they can opt out at any point during the study. Data will be anonymized, and no names or other identifiable features of research participants or users will be disclosed in any manuscript or supplementary material.

Participants (therapy seekers) will be compensated US $10 for completing each survey, one at baseline and one at 3 months follow-up. Participants (therapy seekers) will receive US $30 for completing an in-depth interview. In total, participants are eligible to receive a total of US $50 for completing both surveys and the in-depth interview. Additionally, as a part of participating in this study, participant clients will have the cost of their therapeutic sessions covered, up to 5 sessions and no more than US $600. Therapist participants will be compensated with US $40 for completing the focus group session.

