#### Quantitative Analysis

Quantitative analysis will involve linear mixed-effects models to understand the impact of different treatment doses on mental health outcomes, accounting for repeated measures and potential intragroup correlations. ANOVA will be used to compare the mean outcomes across the dose groups. Because of sample size limitations, we acknowledge that *t* tests and ANOVA may be underpowered to detect the true impact of the intervention on changes in attitudes surrounding therapy. In tandem with the cost analysis, the ANOVA will provide insights into the optimal balance between treatment effectiveness and cost, guiding resource allocation and decision-making for culturally responsive mental health services delivered through the ShockTalk app.

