### Conclusions

The disproportionate burden of mental health disorders among urban Indigenous community members highlights the critical need for innovative and culturally responsive health care delivery systems. ShockTalk, as the first tele–mental health care linkage app designed specifically for Indigenous individuals, represents a promising intervention to bridge this gap. This pilot study’s comprehensive evaluation of ShockTalk will provide valuable insights into how culturally responsive, technology-mediated mental health treatments can be optimized and tailored to meet the unique needs of Indigenous clients in urban settings. By assessing different intensities of engagement and their associated costs, this research aims to identify the most effective and economically viable treatment strategies.

The findings from this study are poised to significantly contribute to the field of Indigenous tele–mental health care by demonstrating the potential benefits of integrating culturally relevant telehealth services into broader mental health support frameworks. By examining variations in treatment doses and their impact on client trust, engagement, and overall satisfaction, we aim to delineate the most effective approaches for delivering mental health care that is culturally appropriate and accessible to this population. The integration of a cost-effectiveness analysis further ensures that the proposed solutions are sustainable and scalable. Future expansions of this research, supported by additional funding, will extend these insights to a larger and more diverse subset of the urban Indigenous population, ultimately guiding policy and practice toward more equitable mental health care provisions.

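### Session attendance both defines the dose strata and forms part of the engagement outcome reported within them, so its difference by dose is built in

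*Protocol article*

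**What the plan says.** All but one of the relevant statements stand in the protocol article under Planned Analysis, Cost Analysis.

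- **Grouping variable.** The section says "Clients’ level of engagement will be characterized by treatment dose" and gives dose as "treatment dose, defined as the number of therapy sessions completed during the 3-month period".
- **Reporting by group.** It continues: "we will descriptively report outcomes stratified by dose (eg, 1-2 sessions and 3-5 sessions), no inferential comparisons across groups will be made".
- **Outcomes.** The primary outcome is change in attitudes on the ATSPPH-SF. For the rest, "Secondary outcomes include trust in technology and telemedicine, measured via the PATAT", together with "client engagement, operationalized through session attendance and app interaction data". None of these is excluded from the report by dose.

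The Conclusions section of the Discussion then states the intended reading: "By examining variations in treatment doses and their impact on client trust, engagement, and overall satisfaction", with the aim of identifying the most effective ways to deliver care.

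**The concern.** Engagement is first defined as dose, then listed as an outcome to be shown by dose, and finally described as something dose acts on. For the attendance component, the first and last of these are the same quantity. A table of attendance by dose group will always show a clear upward step, and that step says nothing about ShockTalk, its therapists or its clients. It only restates how the groups were formed.

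At stake is how a reader takes the engagement row of that table. Beside attitude and trust scores, which could go either way, an engagement row that always rises with dose would look like support for higher dose. If attendance and app interaction were merged into one score, the artefact would be harder to see but still present.

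**Working it through.** There is no planned figure to reproduce. The sample size is pragmatic and the article states no expected relation between dose and engagement. The check is therefore of the structure, followed by its size under stated assumptions.

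**Inputs from the article.** Dose is completed sessions in 3 months, with example strata 1-2 and 3-5 and a funded maximum of 5 sessions (Cost Analysis; Ethical Considerations). The plan is for 10 clients, 5 per arm (Methods, Overview), and 4 clients were enrolled (Results).

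**Step 1: bounds, taking attendance as a session count from 1 to 5.** The lower stratum mean lies between 1 and 2, and the upper between 3 and 5.
- Smallest gap: 3 − 2 = 1 session.
- Largest gap: 5 − 1 = 4 sessions.

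Enumerating every possible set of counts with both strata filled (50 sets for 4 clients, 99 for 5, 924 for 10) gave the same range, 1 to 4, each time. The cut at 2 is only an example in the article, but any cut on the same count gives a gap of at least 1.

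**Step 2: share of variation, under an assumption the article does not make.** Let sessions be uniform on 1 to 5.
- Overall mean 3; variance (4 + 1 + 0 + 1 + 4)/5 = 2.
- Lower stratum: probability 0.4, mean 1.5. Upper stratum: probability 0.6, mean 4. Expected gap 4 − 1.5 = 2.5 sessions.
- Between-stratum variance: 0.4 × (1.5 − 3)² + 0.6 × (4 − 3)² = 0.9 + 0.6 = 1.5.
- Eta-squared for attendance: 1.5/2 = 0.75.

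**Step 3: a combined score.** Add standardised attendance to standardised app interaction with equal weight, and let app interaction be unrelated to sessions (again an assumption). The score has variance 1 + 1 = 2, and the between-stratum part is 0.75, so eta-squared is 0.75/2 = 0.375. Half the artefact survives although app use has no relation to dose.

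**Step 4: what a two-group ANOVA would do.** This was simulated under the same assumptions at the 0.05 level, with at least 2 clients in each stratum:

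| Outcome by dose | Eta-squared | Rejects, 5 clients | Rejects, 10 clients |
|---|---|---|---|
| Attendance | 0.75 | about 67% | about 100% |
| Equal-weight composite | 0.38 | about 25% | about 54% |
| App interaction alone | about 0 | about 5% | about 5% |

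The last row shows that once attendance is removed, the built-in difference disappears. The ANOVA columns show the size of the artefact only, since the article does not say that engagement will be tested this way.

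**The case against.** Several points can be made for the plan, and some of them stand.

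- **Engagement is more than attendance.** This stands. App interaction does not define the strata, so a reader who infers that engagement by dose is wholly true by construction, or can show nothing about ShockTalk, goes further than the text allows. Attitudes and trust by dose do not overlap with the grouping variable either.
- **Attendance is not defined.** This stands in part. If it meant attended over scheduled sessions, a client with 2 of 2 (100%) could exceed one with 3 of 5 (60%), and the strata could overlap. The article does not say this, and it separately equates level of engagement with dose.
- **The report is descriptive.** The Cost Analysis section says so, and that limits the harm. A built-in step still misleads in a descriptive table, and the Conclusions call the relation an impact. The Quantitative Analysis section says "ANOVA will be used to compare the mean outcomes across the dose groups", but it speaks there of mental health outcomes and attitudes, not engagement. Its conflict with the promise of no inferential comparison is a separate matter that must be reconciled.

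Two stronger readings are tempting but not supported. First, one might hold that the comparison would be circular even if dose were assigned. It would not: attendance by assigned dose measures adherence. The circularity arises because dose is defined by completion. Second, one might infer from the cover of "up to 5 sessions and no more than US $600" that therapist fees decide the stratum. The article gives no fee, does not say that therapy ends when cover does, counts completed rather than covered sessions, and offers the strata only as examples.

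**Conclusion.** The point holds for the session-attendance component and is minor. Taken as a count, attendance must differ between the 1-2 and 3-5 groups by 1 to 4 sessions, with no overlap. That result rests only on the article's definitions and on attendance being a count. The figures of 0.75 for attendance and about 0.38 for an equal-weight composite rest further on uniform session counts and on app use unrelated to dose; they show the order of size and are not predictions.

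Nothing here undermines attendance as a feasibility outcome over all clients, or the other outcomes described by dose. With 4 clients enrolled and analysis reported as complete, what remains open is how the results are presented and worded.

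**What to change.** 1. In the Cost Analysis section, remove session attendance from the outcomes reported by dose. Report it once, as a feasibility outcome over all clients offered access.
2. If engagement is still described by dose, use app interaction data alone, as a separate measure not combined with attendance.
3. In the Conclusions, delete engagement from the sentence on the impact of dose, or restrict it to app interaction and call the relation an association.

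These are changes of wording and table layout and need no new data. The cost is one fewer reported dose relation.
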